### Data collection

Study data collectors will collect data regarding MNCH services participants received. All data will be collected using a structured questionnaire by interviewer-facilitated tablet-based face-to-face interviews or abstracted from HBRs (MCH handbook in intervention arm or prenatal card and child health card in the control arm). However, where there is no record of MNCH services received in HBRs, mother’s report of service utilisation will be used in place of the missing information as previously reported by Croft et al. [28]. Data collection will be conducted at participants’ home or at a location of her choice at two time points—at baseline and at 3 months postpartum. Table 3 shows the data collection timeline for each outcome measure.

**Table 3 Tab3:** Data collection timeline for each outcome measure

Time point	Item	Data source		Location
		Survey form	HBR	
Baseline	Participant identification	x		Healthcare facility
	Socio-demographic information	x		Participants home
	Pregnancy history	x	x	
	Household characteristics	x		
	Health behaviour	x		
	ANC utilisation	x	x	
	HBR ownership and utilisation	x	x	
Follow-up (3 months postpartum)	Participant identification	x		Participants home
	HBR ownership and utilisation	x	x	
	Health behaviour	x		
	ANC attendance and maternal health	x	x	
	Infant health and feeding practices	x		
	HBR transcripts		x	

*HBR* home-based record, *ANC* antenatal care

The baseline survey will comprise eight sections designed to elicit responses on socio-demographic factors, household characteristics, pregnancy history, maternal health behaviour and HBR ownership and utilisation. Data regarding ANC attendance, maternal health behaviour, pregnancy outcomes, infant feeding practices and infant and maternal health will also be collected from women retrospectively during the follow-up survey at 3 months postpartum. Verbal responses obtained from mothers will be double-checked against record entries made in the HBRs. In cases where discrepancies occur between the mother’s report and HBR records, the latter will be prioritised. Additionally, we will verify the quality of HBR records by referring to the facility logbook data collected from a randomly selected sub-sample of women.

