**Secondary outcomes**				
Rate of MNCH service utilisation	Total no. of actual MCH service used per person per arm compared with an expected minimum number of service utilisation. Estimate means for each arm	Continuous	No. of ANC services	No. of women with a minimum number of ANC in each arm
			Facility delivery	No of women with facility delivery in each arm
			PNC_mother	No. of women with mother PNC record in each arm
			PNC_child	No. of women with child PNC record in each arm
			Vaccination	No. of women with child vacc record in each arm
Complete CoC (service-based)	Time-dependent composite outcome. Composite outcome including ≥ 4 ANC visits + facility-based delivery + PNC of mother and newborn + complete child immunisation up to 2~3 months. Complete CoC = 1 when all indicators = 1	Binary	First ANC timing	Timeline divided into ≤ 20, 21~30, 31~37 and 38 weeks~ ga
			No. of ANC services	< 4 = 0, ≥ 4 = 1 (≤ 20 weeks); < 3 = 0, ≥ 3 = 1 (21–30 weeks); < 2 = 0, ≥ 2 = 1 (31~37 weeks); < 1 = 0, ≥ 1 = 1 (38 weeks)
			Facility delivery	No = 0; yes = 1
			PNC_mother	No HBR record = 0; HBR record = 1
			PNC_child	No HBR record = 0; HBR record = 1
			Vaccination	< 7 records = 0; 7 records = 1
Neonatal mortality	No. of deaths within the first 28 days of life compared to the total number of deliveries in each study arm. NM = 1 when all indicators = 1	Binary	Live birth	No = 0; yes = 1
			Infant death	No = 0; yes = 1
			Date of death	Death within 28 days of birth = 1
ANC service utilisation	No. of women who receive ≥ 4 ANC visits in each arm regardless of the timing of first ANC. Adequate ANC = 1 if no. of ANC services = 1	Binary	First ANC timing	1st trimester, 2nd trimester, 3rd trimester
			Received ANC	No = 0; yes = 1
			No. of ANC services	< 4 = 0; ≥ 4 = 1
	No. of women who receive ≥ 8 ANC visits in each arm regardless of the timing of first ANC. Adequate ANC = 1 if no. of ANC services = 1	Binary	First ANC timing	1st trimester, 2nd trimester, 3rd trimester
			Received ANC	No = 0; yes = 1
			No. of ANC services	< 8 = 0; ≥ 8 = 1
Facility-based delivery	No. of facility-based deliveries in each arm.	Binary	Facility delivery	No = 0; yes = 1
Infant health check-up	Presence of at least one HBR entry from baby-well clinic attendance.	Binary	Record entry for any of current wgt, polio1, pentavalent, pneumo1 or rota1	No HBR record = 0; HBR record (for any of current wgt, polio1, pentavalent, pneumo1 or rota1) = 1

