Maternal morbidity and pregnancy complication detection rate	No. of cases of specified disease conditions and pregnancy complications diagnosed by an HCP in each arm. Maternal morbidity = 1 if any indicator = 1	Binary	High blood pressure	No HBR record = 0; HBR record = 1
			Preeclampsia	No HBR record = 0; HBR record = 1
			Miscarriage	No HBR record = 0; HBR record = 1
			Stillbirth	No HBR record = 0; HBR record = 1
			Vaginal bleeding	No HBR record = 0; HBR record = 1
			Anaemia	No HBR record = 0; HBR record = 1
			Malaria	No HBR record = 0; HBR record = 1
			TB	No HBR record = 0; HBR record = 1
			HIV	No HBR record = 0; HBR record = 1
			Diabetes	No HBR record = 0; HBR record = 1
Infant morbidity rate	Total no. of disease cases attended by an HCP. Infant morbidity = 1 if all indicators = 1	Binary	Past month sickness	No = 0; yes = 1
			Sought treatment	No = 0; yes = 1
			Treatment from HP	No = 0; yes = 1
Infant mortality	No of deaths of infants < 1 year old compared to the total number of deliveries in each study arm. IM = 1 when if both indicators = 1	Binary	Livebirth	No = 0; yes = 1
			Infant death	No = 0; yes = 1
Maternal health behaviour	Prevalence of maternal health behaviour between arms with regard to tobacco use, alcohol use, PMTCT, malaria prevention, use of ITNs and family planning. Prevalence of each indicator will be compared between the intervention and control arms.	Binary	Current alcohol use	No = 0; yes = 1
			Current tobacco use	No = 0; yes = 1
			PMTCT	No = 0; yes = 1
			Family planning use	No = 0; yes = 1
			Knowledge change tobacco use	No = 0; yes = 1
			Knowledge change alcohol use	No = 0; yes = 1
Malaria prevention		Binary	ITN possession	No = 0; yes = 1
			ITN use	No = 0; yes = 1
			Malaria prophylaxis use	No = 0; yes = 1
Maternal depression	No. of cases of maternal postnatal depressive symptoms in each arm.	Binary	EPDS	< 10 = 0; ≥ 10 = 1
Infant feeding practices	Appropriate infant feeding practices including EIBF, EBF and absence of pre-lacteal feeding. Adequate if all indicators = 1	Binary	EIBF	After 1 h = 0; within 1 h = 1
			Pre-lacteal feeding	Yes = 0; no = 1
			Current BF	No = 0; yes = 1
Child vaccination	Composite outcome for the no. of complete fully vaccinated children at 3 months in each study arm. Vaccination = 1 if all indicators = 1	Binary	Polio0	No HBR record = 0; HBR record = 1
			BCG	No HBR record = 0; HBR record = 1
			Hepatitis B	N HBR record = 0; HBR record = 1
			Polio1	No HBR record = 0; HBR record = 1

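### The maternal morbidity composite pools recorded diagnoses with miscarriage and stillbirth, so a change in it cannot be read as benefit or harm, and pregnancy loss has no outcome of its own

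*Protocol article*

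**What the plan says.** Table 4 lists the secondary outcome "Maternal morbidity and pregnancy complication detection rate" and defines it as "No. of cases of specified disease conditions and pregnancy complications diagnosed by an HCP in each arm". It is typed as binary, with the rule "Maternal morbidity = 1 if any indicator = 1".

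The ten indicators are "High blood pressure", preeclampsia, miscarriage, stillbirth, vaginal bleeding, anaemia, malaria, TB, HIV and diabetes. Each is coded 1 if the home-based record (HBR) has an entry and 0 if it has none. The list under Other secondary outcomes repeats the outcome as a number of provider-diagnosed cases. Neither place says which direction is favourable.

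Three other parts of the protocol bear on this:
- **Mortality rows of Table 4.** Live birth is one of the required indicators for neonatal mortality ("NM = 1 when all indicators = 1") and for infant mortality ("IM = 1 when if both indicators = 1").
- **Maternal health behaviour row of Table 4.** It adds "Prevalence of each indicator will be compared between the intervention and control arms". The morbidity row has no such sentence.
- **Data collection.** At the 3-month survey, "pregnancy outcomes, infant feeding practices and infant and maternal health will also be collected from women retrospectively".

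**The concern.** The name and the variable label pull apart. A detection rate suggests that higher is better, while a variable called maternal morbidity suggests that higher is worse. For the eight diagnoses or signs, the first reading is at least plausible: Outcome measures hypothesises better health-seeking, and more contact with providers can put more diagnoses on record. For miscarriage and stillbirth, a true increase is harm. An any-of-ten rule cannot keep the two apart.

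This matters because no other outcome in Table 4 or under Other secondary outcomes reports fetal loss. A stillbirth scores 0 on both mortality rows, the same score as a surviving infant. If the rule is followed as written, a rise could be reported as more morbidity when detection improved, or as better detection when losses rose. The results are meant to inform a national scale-up decision.

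**Working it through.** The plan states no rate, effect or power for this outcome, so there is no figure to reproduce; the power table in Appendix 3 concerns continuum-of-care completion only. What follows is an illustration with assumed rates.

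**Inputs (all assumptions).** D is the probability of at least one of the eight recorded diagnoses or signs, varied from 10% to 50%. L is the probability of a recorded miscarriage or stillbirth, 3% at reference. D and L are taken as independent.

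**Formula.** From the any-of-ten rule, composite = 1 − (1 − D)(1 − L).

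**Dilution.** Let L double from 3% to 6% with D unchanged.
- D = 30%: 1 − 0.70 × 0.97 = 32.1%, then 1 − 0.70 × 0.94 = 34.2%. That is +2.1 points, and 34.2/32.1 gives a ratio of about 1.07. Loss on its own would show +3.0 points and a ratio of 2.0.
- D = 10%: 12.7% to 15.4%, +2.7 points.
- D = 20%: 22.4% to 24.8%, +2.4 points.
- D = 50%: 51.5% to 53.0%, +1.5 points.

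**Masking.** The composite stays unchanged when the new D equals 1 − (1 − D)(1 − L_old)/(1 − L_new).
- Loss doubles from 3% to 6%, D = 30%: 1 − 0.679/0.94 = 27.8%. A fall in detection of 2.2 points hides the doubling. Across D = 10% to 50% the fall needed runs from 2.9 down to 1.6 points.
- Loss halves from 3% to 1.5%, D = 30%: 1 − 0.679/0.985 = 31.1%. A rise in detection of 1.1 points hides the halving. Across D = 10% to 50% the rise needed runs from 1.4 down to 0.8 points.

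**Ambiguity.** Take a control-arm composite of 32.1% and let detection in the intervention arm rise from 30% to 36%.
- Loss halved: 1 − 0.64 × 0.985 = 37.0%.
- Loss unchanged: 1 − 0.64 × 0.97 = 37.9%.
- Loss doubled: 1 − 0.64 × 0.94 = 39.8%.

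All three are rises, so the composite alone does not tell them apart.

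**The sign does depend on the rates.** At D = 40% and L = 3% the composite is 1 − 0.60 × 0.97 = 41.8%. If loss halves to 1.5% and detection rises only to 40.5%, it falls to 1 − 0.595 × 0.985 = 41.4%. The break-even is D = 1 − 0.582/0.985 = 40.9%, a rise of about 0.9 points.

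**The case against.** The strongest reply has four parts.

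- **The data exist.** Live-birth status is an indicator in both mortality rows, pregnancy outcomes are collected at 3 months, and all ten indicators are coded singly. This stands. A reader might infer that the trial cannot measure fetal loss at all, and the documents do not support that. What is missing is a defined outcome that reports it.
- **Display by component can be left to an analysis plan.** This stands as far as display goes, and the wording about numbers of cases is compatible with counts by condition. The binary rule is nevertheless fixed in Table 4, and its make-up is the point here.
- **The opposed directions are an inference.** This stands in part. The hypothesis under Outcome measures is general and gives no direction for pregnancy loss. Miscarriage and stillbirth are also coded from HBR entries, so fuller recording could raise them, while malaria could fall through prevention. A reader might infer that success must push the variable two ways, or that it must rise when detection improves. Neither is documented, and the break-even above shows that the sign depends on the sizes. The ambiguity remains, and recording differences between two kinds of HBR add to it.
- **The stakes are limited.** This stands. It is one secondary outcome among many. A reader might infer that the third objective cannot be answered, but that objective also draws on mortality, infant morbidity, depression, feeding and vaccination.

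**Conclusion.** The point holds as a badly fixed rule for one secondary outcome. A change in the composite cannot be read as benefit or harm, and a change in pregnancy loss is diluted or can be masked. Under the assumed rates, a doubling of loss from 3% to 6% appears as 1.5 to 2.7 points, and a shift in detection of about 2 to 3 points the other way cancels it. Those sizes rest on assumed rates and on independence. That detected disease and pregnancy loss are pooled follows from Table 4 alone. The primary continuum-of-care comparison is untouched. It is worth changing because the remedy uses data that the trial already plans to collect.

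**What to change.** In Table 4 and the list under Other secondary outcomes:

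1. Remove miscarriage and stillbirth from the composite.
2. Report stillbirth by arm over all births, taken from the pregnancy outcome collected at 3 months and not only from HBR entries, because the two arms use different records.
3. Report miscarriage separately among women enrolled while pregnant. State that it misses losses before enrolment and depends on gestational age at enrolment, and show that age by arm. Participant cohort expects most first visits in the second trimester, and Eligibility criteria also admits mothers.
4. Keep the other eight conditions as a detection outcome, shown condition by condition and not interpreted as morbidity.

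The cost is a change of wording, two more rows and no new data collection. The downsides are one or two more secondary comparisons and a miscarriage figure that can bear only limited interpretation.

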### Other secondary outcomes

Rate of MNCH service utilisation—number of actual MNCH service usedNeonatal mortality—number of infant deaths within the first 28 days of lifeANC service utilisation—frequency of ANC service use in each armFacility-based delivery—number of facility-based deliveries in each armInfant health check-up—proportion of children who received infant health checksMaternal morbidity and pregnancy complication detection rate—number of cases of specified disease conditions and pregnancy complications diagnosed by a health care providerInfant morbidity rate—number of specific childhood disease cases attended by a health care providerInfant mortality—number of infant deaths in each study armMaternal health behaviour—prevalence of maternal health behaviour between arms measured using at baseline and follow-upMaternal depression—number of cases of maternal postnatal depressive symptomsInfant feeding practices—prevalence of appropriate infant feeding practices in each study armChild vaccination—number of fully vaccinated children at the end of the study period

All outcomes will be assessed at follow-up except otherwise stated, and data will be collected through structured interviews and abstracted from HBRs.

The minimum number of MNCH services required for maternal behaviour-based CoC completion is shown in Table 5 and will depend on the timing of the first ANC visit and exposure to the intervention.

**Table 5 Tab5:** Minimum expected number of service utilisation to achieve complete CoC (primary outcome)

Time of first ANC (weeks)	ANC	Del	PNCm	PNCc	Vacc	Total	Complete CoC
≤ 20	4	1	1	1	2	9	4 ANC, del., PNCm, PNCc, 2 vacc visits
21~30	3	1	1	1	2	8	3 ANC, del., PNCm, PNCc, 2 vacc visits
31~37	2	1	1	1	2	7	2 ANC, del., PNCm, PNCc, 2 vacc visits
38~	1	1	1	1	2	6	1 ANC, del., PNCm, PNCc, 2 vacc visits

*ANC* antenatal care, *del.* facility delivery, *PNCm* postnatal care for mother, *PNCc* postnatal care for child, *vacc* two vaccination clinic visits at birth and 2 months infant age

### Statistical analysis

The intervention arm (MCH handbook) will be compared to the control (traditional use of two stand-alone HBRs) in the main analysis. We will conduct descriptive analysis, and baseline data from the intervention and control arms will be analysed for comparability of baseline characteristics. Rates of missing data for each variable will be determined to assess the differences between the arms, and overall losses to follow-up will be determined. We will report reasons for losses within each arm and compare the reasons qualitatively.

We plan to measure intervention impact using two analysis sets: the intention-to-treat (ITT) set and the per-protocol analysis set (PPS). The ITT population will include all participants within the randomised municipalities analysed according to the municipality where they were first registered to receive MNCH services (i.e. discounting where they received second, third or fourth MNCH services) [33, 34]. The ITT population will be the primary analysis set, and all analyses will be conducted using this population unless otherwise stated. In the PPS, participant data will be analysed according to the treatment they actually received. Data from the participant with more than one MCNH service utilisation in the control arm will be included in the control arm regardless of the municipality of first registration for MNCH services in the PPS analysis.

The primary endpoint in this impact evaluation study is to compare the proportion of CoC completion achieved among mothers who received the MCH handbook in the intervention arm and those who received the traditional stand-alone HBRs in the control arm. We will evaluate the effect of the provision of MCH handbooks on CoC completion at the municipality level using a generalised linear mixed model (GLMM) assuming logit link and binomial distribution. All analyses will be based on complete case analysis. Regarding the number of healthcare service utilisations, the analysis will be conducted using survival analysis. We will also evaluate the intervention effects in a subgroup of participants based on socio-economic status, urban/rural residence and other baseline characteristics while accounting for cluster effect.

All analyses will be done using STATA (version 13 or higher, Stata Press, College Station, TX).

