#### Pregnant women/mothers

The MCH handbook will be provided to the participant cohort during their first visit to receive MNCH services in each participating healthcare facility in the intervention arm. Explanation will be given on when and how to use the MCH handbook and on data recording. Participants will also receive health education based on the contents of the MCH handbook. Pregnant women and mothers in the study cohort attending healthcare facilities in control municipalities will continue to benefit from the traditional use of two stand-alone HBRs—the prenatal card and child health card. Pregnant women and mothers in both intervention and control municipalities will be asked to bring their MCH handbook or prenatal card and child health card to every occasion of MNCH service consultation. If a participant in either arm forgot to bring her handbook/card during a consultation, the attending healthcare provider will make a copy of the relevant recording page which will be used for keeping the record of the consultation and given to the participant.

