### Outcome measures

The primary outcome for this study is a measure MNCH service utilisation assessed via the proportion of women who achieved time-dependent maternal behaviour-based CoC completion as at 3 months postpartum. MNCH service utilisation and CoC completion among women in low- and middle-income countries have been found to be associated with many factors such traditional and familial beliefs, distance to healthcare facility [29, 30], health care cost [29–31], maternal education [30], perceived quality of care [29, 31] and service availability [32]. Therefore, factors influencing CoC completion may depend either on maternal behaviour and characteristics (demand-side factors) or service availability (supply-side factors). In this study, we hypothesise that distribution and utilisation of the MCH handbook will lead to maternal behaviour change leading to improved health-seeking behaviour and MCH outcomes. Consequently, the primary outcome is a time-dependent maternal behaviour-based measure of CoC completion. CoC completion will be assessed among all pregnant women who were recruited to the study during their ANC attendance. Under this measure, a time-dependent service utilisation-based CoC completion will be achieved when pregnant women receive MNCH services including a minimum number of ANC visits, facility-based delivery, postnatal care (PNC) for mother and newborn, and child vaccinations at two time points—at birth and at 2~3 months of infant age. MNCH service utilisation assessed via the proportion of women who achieve time-dependent service-based CoC completion as at 3 months postpartum will be assessed as a secondary outcome. Coverage under this measure would depend on supply-side factors, such as service availability. Thus, CoC completion will be achieved only when pregnant women/mothers have received all the required MNCH services as shown in Table 4. Details of other secondary outcomes to be assessed are presented in Table 4.

**Table 4 Tab4:** List of outcomes and definition of outcome indicators

Outcome	Definition	Type	Indicators	Details

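### The per-protocol set counts intervention women as control once they use two control-arm services, which contradicts its own principle and selects on service use

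*Protocol article*

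**What the plan says.** The Statistical analysis section names two analysis sets. In the ITT set, women are "analysed according to the municipality where they were first registered to receive MNCH services", and later visits elsewhere are disregarded. "The ITT population will be the primary analysis set".

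For the second set the principle is: "In the PPS, participant data will be analysed according to the treatment they actually received". The next sentence gives a specific rule: participants with "more than one MCNH service utilisation in the control arm will be included in the control arm regardless of the municipality of first registration". There is no corresponding sentence for use of intervention-arm services.

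Two other parts of the protocol bear on this:

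- **When treatment is received.** Under Pregnant women/mothers: "The MCH handbook will be provided to the participant cohort during their first visit to receive MNCH services" in intervention facilities, together with explanation and health education. Women in both arms "will be asked to bring their MCH handbook or prenatal card and child health card to every occasion of MNCH service consultation".
- **What the outcome is made of.** Under Outcome measures: "The primary outcome for this study is a measure MNCH service utilisation". Table 5 requires 9, 8, 7 or 6 services in total for complete CoC, depending on when antenatal care began.

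**The concern.** There are three problems with the rule as written.

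1. **It conflicts with the stated principle.** A woman who registers in an intervention municipality has the handbook from that visit and carries it afterwards. If she later uses two services in a control municipality, she is analysed as control although she received the handbook.
2. **It is asymmetric.** Two control-arm services move a woman into control. No number of intervention-arm services is said to move a woman into intervention.
3. **Its trigger is built from outcome components.** Antenatal visits, delivery, postnatal care and vaccination visits are what the rule counts and also what the primary composite counts. Being moved therefore depends on how much care a woman uses after allocation.

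At stake is how the PPS can be read beside the ITT result. Disagreement between the two could come from the grouping rule alone.

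**Working it through.** No figure in the protocol depends on this rule, so there is none to reproduce.

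**Step 1: who can be moved.** Inputs are the first visit in an intervention facility (Pregnant women/mothers), a trigger of at least 2 control-arm services (Statistical analysis) and the CoC totals in Table 5.

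- Minimum services needed to be moved: 1 + 2 = 3.
- Women with 1 or 2 services in total cannot be moved.
- Complete CoC needs at least 6 services, so those women all have CoC = 0 and all stay in the intervention group.

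**Step 2: the effect on the comparison.** Take equal arms, no true effect, CoC proportion p in both arms, a fraction f of intervention women moved, and CoC proportion c among those moved.

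- PPS intervention: (p - f c)/(1 - f)
- PPS control: (p + f c)/(1 + f)
- Difference: 2f(p - c)/(1 - f²)

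The sign depends only on whether c is above or below p. Step 1 pushes c above p, because the lowest users are excluded from the moved group. It does not guarantee this, because women who cross may differ from other women.

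**Step 3: plausible size.** The simulation used 2,000,000 women with p = 15% in both arms, the control rate in the Power analysis section. The following are assumptions that the documents do not give:

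- first antenatal visit by 20 weeks, so 9 services needed, with that visit at the registering facility;
- between-woman standard deviation of 1.5 on the logit scale;
- 5% to 30% of women crossing, independently of their tendency to use care;
- 30%, 50% or 80% of crossers' later visits made in the other arm.

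PPS difference, intervention minus control, in percentage points:

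| Women crossing | 30% of later visits | 50% | 80% |
|---|---|---|---|
| 5% | -0.55 | -0.51 | -0.17 |
| 10% | -1.05 | -0.88 | -0.50 |
| 20% | -1.91 | -1.85 | -1.01 |
| 30% | -2.82 | -2.80 | -1.62 |

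The ITT difference in the same runs stayed within 0.12 points of zero, so the smallest entry is close to simulation noise. Moved women had CoC of about 18% to 27%.

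Check of the formula on one cell (10% crossing, 50% of later visits), where f = 6.67% and c = 21.72%: 2 × 0.0667 × (0.15 - 0.2172)/(1 - 0.0667²) = -0.0090, or -0.9 points, against -0.88 simulated.

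**Step 4: symmetry.** With a mirror rule added (20% crossing, 50% of later visits), the PPS gave 15.01% v 15.04%, a difference of -0.03 points. Symmetry removes the bias under these null assumptions, but women are still classified by service use after allocation.

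**The case against.** **Treatment is more than the handbook.** The Intervention section describes a package of handbook distribution, provider training and community mobilisation. Control-arm providers are trained only on dating the pregnancy. A woman who takes repeated care in control facilities therefore has mixed exposure, and place of care is one possible way to classify her. It stands that mixed exposure needs a rule. It does not rescue this one: read literally, a woman with seven services in intervention facilities and two in control facilities is analysed as control.

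**The rule is not absolutely one-way.** A woman registered in control who uses one control service, then attends an intervention facility and receives the handbook, does not trigger the rule. The general principle would place her in intervention. This stands, and a reader should not infer that no control woman can ever change group. The simulation did not model this path. With two control-arm services, however, she stays in control even if she later obtains a handbook.

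**The direction is not proven.** The protocol names distance and service availability as influences on use of care. Women with split care might complete CoC less often than average, and the sign would then reverse. This stands: the direction is probable, not known.

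**A larger bias might be inferred.** If 10% of intervention women were moved and 30% of them had complete CoC, the formula gives 13.3% v 16.4%, or -3.0 points. The arithmetic is right, but 30% lies above the simulated 18% to 27%. With those values and 10% moved, the difference is -0.6 to -2.4 points.

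**Analysis-set detail may sit in a fuller document.** That would answer a complaint of omission. Here the rule is stated, and the problem is what it states.

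**Conclusion.** The PPS rule is wrong as written. It contradicts the principle in the sentence before it, treats the two arms unequally, and conditions on components of the primary outcome. The misgrouping and the three-service threshold follow from the text alone.

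Bias against the handbook is likely but rests on crossers not being unusually low users of care. The range of about -0.2 to -2.8 points is illustrative, because the documents give neither the crossover rate nor CoC among crossers. With little crossover the effect would be negligible.

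A reader might infer that the trial's main result is compromised. The documents do not support that: ITT is the primary set, it groups by first registration, and this rule does not touch it. The damage is confined to the PPS and to its use beside the ITT result.

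**What to change.** Delete the reassignment sentence. Define the PPS within randomised arm by the record issued at first registration: intervention women who were given the handbook and control women who were given the stand-alone cards. Move no one between arms.

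If women with cross-arm care are to be excluded, apply the same rule in both directions as a sensitivity analysis and report the numbers excluded by arm. Label the PPS as supportive, because such an exclusion still conditions on service use after allocation, and symmetry balances it only if crossing is similar in the two arms.

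The cost is a change of wording and possibly a somewhat smaller PPS. Table 3 already lists ownership of the home-based record at baseline and follow-up, so no new data item appears to be needed.
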